### Who will take informed consent? {26a}

Trained study staff collect the informed consent.

### Additional consent provisions for collection and use of participant data and biological specimens {26b}

The process of informed consent includes a discussion of an option to allow the collection and storing of additional biospecimens for future research that may include analyses on genetic material.

## Interventions

### Explanation for the choice of comparators {6b}

Two groups are compared in this study. Group 1 is a standard care plus education control group and was selected because the intervention provides a level of care that is consistent with the typically minimal amount of lifestyle counseling received by women before pregnancy and also is not expected to promote clinically significant weight loss. Group 2 is standard care plus education plus weight loss intervention and was selected in order to isolate the effects of pre-conception weight loss on GDM recurrence and other health outcomes.

### Intervention descriptions {11a}

#### Group 1: Standard care + education

Women in this condition receive usual medical care before and during pregnancy and throughout the trial. Also, these women meet with a study interventionist for 20-min individual sessions at study entry and again after 16 weeks. The first meeting at study entry encourages women to spend the next 16 weeks improving overall health before pregnancy and reviews nutrition (e.g., consuming multivitamins, folic acid) and physical activity recommendations. The second face-to-face meeting occurs after 16 weeks and focuses on managing stress and also includes a *Pregnancy Primer*. Since all women in the study have expressed a desire to have another pregnancy within 1–3 years, this module provides participants with standard information on methods to track ovulation. Participants also receive information on the recommended amount of weight gain [118] during pregnancy. Throughout the study, women receive quarterly study newsletters with study updates and general information about preconception health and wellness.

#### Group 2: Standard care + education + weight loss intervention

##### Overview

This group receives all aspects of group 1 plus a standard lifestyle modification program implemented to induce ≥ 10% weight loss over 16 weeks and promote weight loss maintenance over subsequent months (12–36 months depending on enrollment year) until conception. This comprehensive, individually focused, SCT-based weight control program includes education, behavioral self-regulatory strategies, ongoing contact, feedback, and social support. The intervention is based on the DPP and Look Ahead lifestyle interventions [101, 119, 120], which have been proven effective in promoting significant weight loss and maintenance in multiethnic, English- and Spanish-speaking individuals across the country [119, 120]. The intervention provides guidance and resources for English- and Spanish-speaking individuals from a variety of different cultures and backgrounds.

##### Format and contact

The intervention focuses on ongoing, individual contact with a study interventionist to promote weight loss prior to conception. Visits may be conducted in person, on the phone, or through video conferencing. For the first 16 weeks, participants meet weekly for ~ 30 min. Thereafter, participants meet bi-weekly (or more frequently in the context of weight regain) to maintain weight loss until conception. After conception, intervention contacts are discontinued.

##### Weight loss goals

Participants are given a scale and told to aim for a weight loss of 1–2 lb per week for the first 16 weeks. Patients desiring to lose more weight during the program are encouraged to do so, provided they maintain reasonable eating and activity patterns and do not reduce below normal weight. After 16 weeks, participants may work on weight loss maintenance or continue to lose weight at a moderate rate (1–2 lb/week) until confirmed conception.

##### Dietary goals

Participants are instructed to follow a standard calorie restriction diet used in lifestyle modification programs. Calorie goals are based on study entry weight with 300 cal/day adjustments for breastfeeding status, if applicable. Participants with an entry weight of < 91 kg are prescribed a 1200-kcal/day self-selected diet, and those with an entry weight of > 91 kg are prescribed a 1500-kcal/day. A standard, low-fat diet is prescribed (35% fat, 20% protein, 45% CHO), since prior research has suggested that recurrence of GDM was greater in women who consumed more fat between pregnancies [121]. After the 16-week program, dietary goals may be adjusted to help women maintain their weight loss or weight maintenance goal until conception.

##### Exercise goals

Participants are instructed to increase their physical activity to at least 150 min per week during the initial 16-week program (e.g., 30 min per day, 5 days per week). Thereafter, they are advised of higher goals (60 min/day) to promote long-term weight loss maintenance. Brisk walking, “child-friendly,” and inexpensive activities are suggested, taking into consideration potentially unsafe neighborhoods. Participants are provided with a pedometer and encouraged to gradually increase the number of steps they walk per day (with an increase of ~ 250 steps/day each week) until reaching an ultimate goal of about 10,000 steps per day [122].

##### Behavioral goals

The major features of behavior modification include self-monitoring, behavior chains, stimulus control, goal-setting, self-reinforcement, problem-solving, social assertion, and cognitive strategies [123]. Participants complete weekly behavioral assignments, which are reviewed by the interventionist. Participants are given self-monitoring records or encouraged to use apps, if preferred, to facilitate self-monitoring.

### Criteria for discontinuing or modifying allocated interventions before conception {11b}

Site physicians who are trained in obstetrics/gynecology guide decisions as to whether or not to continue intervention or assessments in women with medical difficulties. If needed, the study physicians contact a participant’s provider to discuss treatment/assessment continuation for participants. The study physicians do not provide medical care during the course of the study but refer and help participants obtain appropriate medical or psychiatric care, if needed. The rate of weight loss and caloric restriction are monitored, and if any extreme and overly rapid weight losses occur, healthier practices are encouraged and adherence to these recommendations is monitored. A subset of women may be breastfeeding upon enrollment. Moderate weight loss does not appear to adversely impact breastfeeding [113, 124], but study staff are monitoring such occurrences and provide referrals, as needed. To reduce the risk of muscle soreness, muscle strain, or joint sprain; loss of balance; or trauma by falling, the physical activity (walking) is moderate, progressive, and volitional, and goals may be modified, as needed for an individual participant.

### Strategies to improve adherence to interventions {11c}

The behavioral weight loss program includes a variety of strategies to improve adherence. These include strategies related to appropriate goal setting, cognitive restructuring, relapse prevention, and problem-solving. In addition, the study interventionist provides support for all positive behavioral changes. Weekly supervision meetings with the intervention team are designed to promote treatment fidelity. Participant cases are reviewed and strategies discussed with the intervention team to promote participant adherence to attending treatment sessions, completing food and exercise records, engaging in daily self-weighing, and following calorie and activity goals. Intervention fidelity measures (coded audiotaped sessions) are further reviewed and discussed to guide and promote adherence.

### Relevant concomitant care permitted or prohibited during the trial {11d}

During the trial, participants are not restricted from receiving concomitant care and/or interventions.

### Provisions for post-trial care {30}

There is no provision for post-trial care. There is no anticipated harm and no compensation for harm due to trial participation.

### Outcomes {12}

#### Primary outcome

The study’s primary outcome is GDM diagnosis in the next pregnancy. The 2-step approach of diagnosing GDM is done at 24–28 weeks’ gestation and involves participants receiving as part of standard care a 50-g oral glucose solution followed by a 1-h venous glucose determination. Participants meeting or exceeding the 1-h screening criteria (a cutoff for an abnormal 1-h screen of ≥ 130 mg/dL) are then referred to the study for completion of the 100-g, 3-h diagnostic oral glucose tolerance test (OGTT). Positive diagnosis of GDM is based on the Carpenter and Coustan criteria [108] based on 2 abnormal values on the 3-h OGTT that includes a fasting value of > 95 mg/dL, 1 h > 180 mg/dL, 2 h > 155 mg/dL, 3 h > 140 mg/dL. The results of the study’s 100-g OGTT are immediately shared with the participants’ medical providers who interpret and inform patients of GDM screening results. If the study measured 100-g, 3-h diagnostic OGTT is not obtained, provider assessments done in standard care that are based on acceptable diagnostic methods (Table 2) are used to diagnose GDM. Final determination of GDM diagnosis is done by an independent evaluation of records from the study’s Ob/Gyn physician-researchers who are masked to the randomized group.

**Table 2 Tab2:** Diagnostic criteria for GDM in Gestational Diabetes Prevention/Prevención de la Diabetes Gestacional

1.	3-h 100 g OGTT performed at ≥ 20 weeks’ gestation in which 2 or more values exceed the criteria as follows: fasting ≥ 95 mg/dL; 1 h ≥ 180 mg/dL; 2 h ≥ 155 mg/dL or 3 h ≥ 140 mg/dL [108]
2.	75 g OGTT performed at ≥ 20 weeks’ gestation and 1 or more values exceed (fasting ≥ 92, 1 h ≥ 180; 2 h ≥ 153) [109]
3.	1-h 50 g test performed at any time during pregnancy with a value ≥ of 200 mg/dL
4.	Fasting glucose value prior to 20 weeks’ gestation ≥ 92 mg/dL and < 125 mg/dL and clinic treats the patient for GDM with medication or insulin
5.	HbA1c conducted anytime during pregnancy with a value ≥ of 5.7% and the clinic treats the patient for GDM with medication or insulin

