### Eligibility criteria {10}

Table 1 describes the eligibility and exclusion criteria for this trial. Participants must have physician documentation of GDM during any prior pregnancy. Given the diversity of clinically acceptable methods used to diagnose GDM [104–107], several diagnostic methods for prior GDM are eligible. Acceptable documentation to confirm prior GDM are as follows: (1) a 3-h 100 g oral glucose tolerance test (OGTT) performed at ≥ 20 weeks’ gestation in which 1 or more values exceeded the Carpenter and Coustan criteria [108] (i.e., fasting ≥ 95 mg/dL; 1 h ≥ 180 mg/dL; 2 h ≥ 155 mg/dL or 3 h ≥ 140 mg/dL), (2) a 75-g OGTT performed at ≥ 20 weeks’ gestation and 1 or more values exceeded the International Association of Diabetes and Pregnancy Study Groups (IADPSG) criteria [109] (i.e., fasting ≥ 92, 1 h ≥ 180; 2 h ≥ 153), (3) a 1-h 50 g test performed at any time during pregnancy with a value of ≥185 mg/dL (if ≥130 mg/dL but < 185 mg/dL and the clinic did not do a follow-up 100-g OGTT, the participant would be ineligible), (4) a fasting glucose value prior to 20 weeks’ gestation was ≥ 92 mg/dL and < 125 mg/dL and treatment with medication or insulin, or (5) an HbA1c conducted anytime during pregnancy with a value of > 5.6% and the treatment with medication or insulin.

**Table 1 Tab1:** Inclusion and exclusion criteria for Gestational Diabetes Prevention/Prevención de la Diabetes Gestacional

Inclusion criteria	Prior diagnosis of GDM
	Planning to have a baby in the next 1–3 years
	BMI > 25 kg/m^2^
	English- or Spanish-speaking
	Breastfeeding or non-breastfeeding
	Literacy ≥5th grade level
	Access to a cell phone
Exclusion criteria	Age < 18 years
	HbA1c test (> 6.5%)
	≥ 3 months postpartum
	Current pregnancy
	Tubal ligation Semi-permanent form of birth control with no plans for removal (e.g., hormonal progesterone intrauterine device or hormonal contraceptive implant)
	Relocating in the next 2 years
	Medications that affect weight or diabetes (e.g., oral corticosteroid and metformin)
	Use of weight loss medications
	Serious current physical disease (e.g., heart disease, cancer, renal disease, and diabetes) for which physician supervision of diet and exercise prescription is needed
	Orthopedic limitations to aerobic exercise
	History or plans of bariatric surgery
	Current problems with drug abuse and/or symptoms of an eating disorder, which occurred less than 3 years year ago

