### Methods in analysis to handle protocol non-adherence and any statistical methods to handle missing data {20c}

Under intention-to-treat principles, all participants with confirmed pregnancy will be included in the primary analysis. If study measured OGTT results are not available, provider assessments will be used (based on chart abstraction). Missing data related to outcomes will be evaluated to assess whether the missing mechanism may be ignorable or non-ignorable [165–167]. If the missing data mechanism is judged to be ignorable, where appropriate, analyses involving mixed models may be used such that all existing values are analyzed, and no observations are deleted due to missing values. Alternatively, multiple imputations may be carried out to create several complete data sets. For each complete data set, overall tests of interest for the outcome will be conducted and the results of each combined to create a single test result. For completeness, a pattern missing analysis will be conducted to investigate non-ignorable missingness. If the missing data mechanism is likely to be non-ignorable, multiple imputations can be conducted using a version of the approximate Bayesian bootstrap based on distance-based selection criteria [168]. Sensitivity analyses under various assumptions regarding the missing data will be conducted to confirm the robustness of the results.

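### The primary-outcome rule for the 100-g OGTT uses > cut-offs in the text and ≥ cut-offs in Table 2, so a result that turns on a cut-off value can be GDM or not depending on who measured it

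*Protocol article*

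**What the plan says.** All references are to the protocol article.

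- **Study-measured test (Outcomes {12}, Primary outcome, text).** GDM is diagnosed "based on 2 abnormal values on the 3-h OGTT that includes a fasting value of > 95 mg/dL, 1 h > 180 mg/dL", then "2 h > 155 mg/dL, 3 h > 140 mg/dL". All four cut-offs are strict.
- **Provider result (same section, Table 2 item 1).** A 100-g test is positive when it is one "in which 2 or more values exceed the criteria as follows: fasting ≥ 95 mg/dL; 1 h ≥ 180 mg/dL", then "2 h ≥ 155 mg/dL or 3 h ≥ 140 mg/dL". The test, the four numbers and the cited reference are those of the text, but the cut-offs are inclusive.
- **When Table 2 applies.** If the study test is not obtained, "provider assessments done in standard care that are based on acceptable diagnostic methods (Table 2) are used to diagnose GDM". The missing-data section {20c} repeats this: "If study measured OGTT results are not available, provider assessments will be used (based on chart abstraction".
- **The same named criteria elsewhere.** Eligibility criteria {10} writes them as "fasting ≥ 95 mg/dL; 1 h ≥ 180 mg/dL; 2 h ≥ 155 mg/dL or 3 h ≥ 140 mg/dL". That section asks for one or more values because it documents a prior pregnancy, so only the inequality sign is comparable.
- **Adjudication.** "Final determination of GDM diagnosis is done by an independent evaluation of records from the study’s Ob/Gyn physician-researchers", who are masked to group. No inequality is stated for them.

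**The concern.** GDM in the next pregnancy is the only primary outcome, and an endpoint rule should classify identical results identically. Read literally, the strict rule governs women with a study OGTT and the inclusive rule governs women whose 100-g OGTT comes from the clinic. Source of measurement then becomes part of the case definition. If a single rule was intended, the text and the table still disagree on what it is. The choice would be left to adjudication or analysis, and a reader of the results could not tell which definition produced them.

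**Working it through.** **1. The two rules side by side (mg/dL)**

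| | Text, study test | Table 2 item 1, provider test |
|---|---|---|
| Fasting | > 95 | ≥ 95 |
| 1 h | > 180 | ≥ 180 |
| 2 h | > 155 | ≥ 155 |
| 3 h | > 140 | ≥ 140 |
| Abnormal values needed | 2 | 2 or more |

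**2. Which results change class**

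Let a be the number of values strictly above their cut-off and b the number exactly equal to it. The text counts a; Table 2 counts a + b. Class changes only when a ≤ 1 and a + b ≥ 2.

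- Fasting 95, 1 h 180, others below: a = 0, b = 2. Not GDM by the text; GDM by Table 2.
- One value clearly raised and one exactly at its cut-off: a = 1, b = 1. The same reversal.
- Two or more values strictly above: GDM under both.

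**3. How often this could happen**

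The article gives no glucose distributions, so the following inputs are assumptions: four-point OGTTs drawn as multivariate normal and rounded to whole mg/dL; base means 90, 175, 150 and 120; base SDs 8, 25, 25 and 25, multiplied by 0.8, 1.0 or 1.3; means shifted by −0.5, 0 or +0.5 SD; common correlation 0.3 or 0.6. This gives 18 scenarios of 1,000,000 tests each.

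- Lowest share changing class: 1.6% (shift −0.5, SD × 1.3, correlation 0.6).
- Central scenario (no shift, SD × 1.0, correlation 0.6): 40.2% positive with ≥ and 37.6% with >, so 2.6% change.
- Highest share: 3.8% (shift +0.5, SD × 0.8, correlation 0.3).

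Applied to the 176 pregnancies in Sample size {14}: 176 × 0.016 = 2.8 and 176 × 0.038 = 6.7, or about 3 to 7 women. This is an upper bound. It assumes that every woman has a 100-g OGTT, whereas only those with a 1-h screen of at least 130 mg/dL are referred for one and others may be classified by Table 2 items 2 to 5. It also compares all-strict with all-inclusive classification, whereas the literal reading mixes the two by source.

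**4. Effect on the comparison between arms**

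Let d be the share of tests that change class, taken as equal in both arms, and let s₁ and s₀ be the shares of intervention and control women classified by the study test. Relative to using ≥ throughout, the arm rates fall by s₁d and s₀d, so the difference between arms moves by (s₁ − s₀)d. If s₁ = s₀, it does not move. With a hypothetical 20-point gap, 0.20 × 1.6 = 0.3 and 0.20 × 3.8 = 0.8 percentage points. The planned difference is 60 − 38 = 22 points.

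**5. Effect on power (background only)**

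Inputs from Sample size {14}: 88 per group, 60% versus 38%, odds ratio 0.43, stated power ≥ 81.98%. Two-sided α = 0.05 is assumed because none is stated. With p̄ the mean of p₁ and p₂:

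power = Φ{[|p₁ − p₂| − 1.96√(2p̄(1 − p̄)/88)] / √([p₁(1 − p₁) + p₂(1 − p₂)]/88)}

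- 60% versus 38%: 83.7%, within 2 points of the stated figure.
- Odds ratio 0.43: p₂ = 0.645/1.645 = 39.2%, power 79.3%.
- Both rates in the odds-ratio case moved together by 1 to 3 points, up or down: 79.3% to 79.5%.

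No sample-size figure depends on the choice of inequality.

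**The case against.** The strongest reply is that this is a drafting slip and one rule was meant throughout. The text and Table 2 item 1 share the test, the numbers and the reference. Table 2 is captioned as the trial's own diagnostic criteria, not as provider criteria only. It pairs a verb meaning to go beyond with a ≥ sign, so the wording of inequalities is loose generally. Masked physicians make the final determination for all women, and nothing instructs them to use different cut-offs by source. All of this is fair, and a slip is quite possible. It does not remove the point: if one rule was meant, the text and the trial's own table still disagree on it, and no sentence says which prevails. Masking guards against biased judgement; it does not choose between two written definitions.

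The objection does succeed against several stronger readings that a reader might infer:

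- **Differential misclassification because the intervention arm has more study contact.** Intervention contacts stop after conception, whereas the OGTT is done at 24–28 weeks. The 26-week assessment, its $50 honorarium and the retention procedures are the same in both arms, and assessors and adjudicators are masked. Earlier contact could still affect attendance, but nothing in the article shows that it does.
- **A control rate drifting away from the definition behind the 60% assumption.** Sample size {14} does not say which diagnostic definition or inequality underlies the 60%.
- **Abnormal fasting glucose made mandatory, or exactly two abnormal values required.** The text lists all four time points in one run. If that list made fasting mandatory it would make all four mandatory, against its own two-value rule. Nor can two abnormal values sensibly exclude three or four.

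**Conclusion.** The point holds as an internal contradiction in the primary-outcome definition. For the same 100-g test, the text and Table 2 item 1 give different inequalities, the two are attached to different sources of measurement, and the adjudicators are given no rule that settles it.

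Its numerical weight is small: about 1.6% to 3.8% of 100-g OGTTs, at most about 3 to 7 of 176 women, probably mostly non-differential, with power essentially unchanged. Those sizes rest on assumed means, SDs and correlations and on whole-number reporting; that a result turning on a cut-off value is classified two ways does not. The case for correcting it is clarity of the endpoint at almost no cost, not a threat to the trial's conclusion. The documents do not establish which inequality was intended. The inclusive form appears in two of the three places, but frequency does not settle it.

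**What to change.** Reconcile the text of Outcomes {12} and Table 2 item 1 to one inequality and one count rule for the 100-g OGTT, with the sponsor confirming which was intended. State that the masked adjudicators apply that single rule to the recorded glucose values from study and clinic 100-g OGTTs alike.

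The cost is a wording change, plus re-reading recorded values for any woman whose result includes a value exactly at a cut-off. Sample size, visits and procedures do not change. As a change to how the outcome is defined, it would follow the article's own route of IRB review and a registry update (section {25}).

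### The primary endpoint mixes non-equivalent GDM definitions according to whether the study OGTT was obtained; if the mix differs by arm, the comparison can be biased in either direction

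*Protocol article*

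**What the plan says.** All of the following is in the protocol article.

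- **Study rule (Outcomes {12}, Primary outcome).** Standard care supplies the 50-g test, with "a cutoff for an abnormal 1-h screen of ≥ 130 mg/dL". Women at or above it are referred to the study for the 100-g OGTT, and GDM is diagnosed "based on 2 abnormal values on the 3-h OGTT that includes a fasting value of > 95 mg/dL", with cut-offs of 180, 155 and 140 mg/dL at 1, 2 and 3 hours.
- **Fallback (same section).** When the study has no 100-g OGTT for a woman, "provider assessments done in standard care that are based on acceptable diagnostic methods", as listed in Table 2, are used. The missing-data section {20c} repeats this: "If study measured OGTT results are not available, provider assessments will be used".
- **Table 2.** Item 1 is a "3-h 100 g OGTT performed at ≥ 20 weeks’ gestation in which 2 or more values exceed the criteria". Item 2 is a 75-g test "and 1 or more values exceed (fasting ≥ 92, 1 h ≥ 180; 2 h ≥ 153"). Item 3 is a 50-g value of at least 200 mg/dL. Items 4 and 5 are an early fasting glucose or an HbA1c result, each combined with treatment by the clinic with medication or insulin.
- **Adjudication.** Study physicians masked to group make the final determination.
- **Early diagnoses (HbA1c tests).** Women with a clinical GDM diagnosis before 24 weeks stay in the analysis.
- **Stratification {16a}.** The strata are site, pre-diabetes status and prior method of GDM diagnosis (one-step 2-h test versus other).
- **Primary model {20a}.** Logistic regression with site and a list of baseline covariates. Prior method of diagnosis is not among those named.

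**The concern.** A woman's case status depends partly on which test happens to exist for her. If her only abnormality is a fasting value of 92 to 94 mg/dL, she is a case under item 2 and cannot be one under the study rule. Conversely, a woman with a 50-g value of 130 to 199 mg/dL and no OGTT of any kind can be a case only through item 4 or 5, which need drug treatment, although the study OGTT might have found her positive.

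Which route applies is settled after randomisation, by whether the study OGTT was done and by how the clinic tests. If the mix of routes differs between arms, part of the observed difference in GDM reflects the test used and not glycaemia. If the mix is the same, the estimate still blends different case definitions and is somewhat diluted.

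Two features of the plan look like safeguards but do not reach this. Masked adjudicators still apply a different rule according to the test on file. The sensitivity analyses promised in {20c} concern missing data, and the fallback makes these women's outcomes non-missing.

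**Working it through.** **1. The plan's own figure.** Sample size {14} gives 88 pregnancies per group, GDM 60% versus 38%, and power of at least 81.98%. No alpha is stated; I assume two-sided 5%. With pooled variance under the null:

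- Pooled proportion (0.60 + 0.38)/2 = 0.49; null SE = √(2 × 0.49 × 0.51 / 88) = 0.0754.
- Alternative SE = √((0.60 × 0.40 + 0.38 × 0.62)/88) = 0.0735.
- Power = Φ((0.22 − 1.96 × 0.0754)/0.0735) = Φ(0.98) = 83.7%.

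This agrees with the stated figure to within 2 points, so it serves as the baseline.

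**2. The routes against the study rule.**

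| Route | Compared with the study rule |
|---|---|
| Item 1 | Same test and number of values; Table 2 writes ≥ where the text writes > (to be reconciled) |
| Item 2 | Looser: no screen, one value, fasting 92 against 95, 2-h 153 against 155 |
| Item 3 | No OGTT needed, but a high 50-g cut-off (200) |
| Items 4, 5 | Different tests, and positive only if the clinic gives drug treatment |

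**3. Model.** Let p be the GDM rate under the two-step rule, m the share of an arm classified by the fallback, f the share of two-step negatives that the fallback counts as GDM, and g the share of two-step positives that it does not count.

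Observed rate = p(1 − m·g) + (1 − p)·m·f

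With the same p in both arms, the spurious difference (control minus intervention) = (m_C − m_I) × [(1 − p)·f − p·g].

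The documents give no m, f or g. All values below are assumptions.

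**4. No true effect, p = 0.5, 88 per arm.**

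| m_C, m_I | f | g | Spurious difference | Two-sided type I error |
|---|---|---|---|---|
| 30%, 10% | 0.1 | 0 | 0.20 × 0.05 = 1.0 point | 5.2% |
| 30%, 10% | 0.2 | 0 | 0.20 × 0.10 = 2.0 | 5.8% |
| 30%, 10% | 0.3 | 0 | 0.20 × 0.15 = 3.0 | 6.8% |
| 40%, 10% | 0.1 | 0 | 0.30 × 0.05 = 1.5 | 5.5% |
| 40%, 10% | 0.2 | 0 | 0.30 × 0.10 = 3.0 | 6.8% |
| 40%, 10% | 0.3 | 0 | 0.30 × 0.15 = 4.5 | 9.2% |
| 30%, 10% | 0.2 | 0.2 | 0.20 × (0.10 − 0.10) = 0 | 5.0% |
| 30%, 10% | 0 | 0.3 | 0.20 × (−0.15) = −3.0 | 6.8% |

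Exchanging the arms' fallback shares reverses every sign.

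**5. Equal use, 20% in both arms, true rates 60% and 38%.**

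- f = 0.2, g = 0: control 0.60 + 0.40 × 0.04 = 61.6%; intervention 0.38 + 0.62 × 0.04 = 40.5%. The difference is 21.1 points and power 80.6%.
- f = g = 0.2: control 0.60 × 0.96 + 0.40 × 0.04 = 59.2%; intervention 0.38 × 0.96 + 0.62 × 0.04 = 39.0%. The difference is 20.2 points and power 77.1%.

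Under the null, equal use creates no difference.

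**The case against.** A reader might infer that the fallback is simply a looser test, that controls will use it more because they have had less study contact, and that the result will therefore favour the intervention. The documents do not support that reading.

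- **Not uniformly looser.** Only item 2 plainly is. Item 1 is essentially the study test, and items 4 and 5 can miss cases.
- **Not mainly a matter of attendance.** The 50-g screen belongs to standard care. A woman who skips the study OGTT after it is already in a two-step pathway, and a provider 100-g test puts her under item 1. A 75-g result reflects a clinic that tests in one step. The study OGTT is also absent, quite properly, when the screen is below 130.
- **Unequal attendance is not documented.** Intervention contacts end at conception. Both arms have brief quarterly assessments until conception, the same reminders and newsletters, and the same $50 for the 26-week visit. Assessors are masked.
- **Stratification helps.** Stratifying by site and prior diagnostic method tends to balance clinic testing practice.

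These points remove the fixed direction and the attendance mechanism. They do not make the definitions equivalent or guarantee equal use.

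It can also be said that a restricted sensitivity analysis and a table of diagnostic route belong in an SAP that is not shown. For the table alone that is fair; it is reporting detail. But the protocol itself fixes the mixed endpoint and names the model covariates. That covariate list is open-ended, so adding the stratum is consistent with it.

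Finally, restricting to one pathway conditions on a post-randomisation event. This stands, and it limits the analysis to a supportive role.

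**Conclusion.** The point holds as a mixed-definition problem of unknown direction. The protocol fixes a primary endpoint whose case definition varies with the test available, and neither masked adjudication nor the missing-data analyses resolve this.

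The size is modest. With a 20 to 30 point difference in fallback use and a purely looser fallback that counts 10 to 30% of two-step negatives, the spurious difference is about 1 to 4.5 points and type I error 5.2 to 9.2%. It is zero when use is equal or when over- and under-counting offset, and it reverses when the fallback mainly misses cases. Equal use at 20% takes the 22-point design difference to between 20 and 21 points in the scenarios shown. Every input on fallback use and misclassification is assumed, and nothing in the protocol shows that the arms will differ. The case for acting is that the remedy is cheap, and that without it a reader could not separate an effect on glycaemia from an effect of which test was used.

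**What to change.** Keep the fallback and keep all women with a confirmed pregnancy in the primary analysis, so that no outcomes are lost. Then:

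1. Add prior method of GDM diagnosis (one-step 2-h test versus other) to the primary logistic model in {20a}. It is already a randomisation stratum and plausibly predicts the clinic's test. As a two-level factor it costs one coefficient and no new data.
2. Pre-specify a supportive sensitivity analysis on one common definition: women classified by the two-step 100-g pathway, whether done by the study or a provider, with those below the 50-g screening cut-off counted as non-GDM. Show it beside the diagnostic route by arm.
3. Reconcile the > in the text with the ≥ in Table 2 for the 100-g thresholds, so that the common definition is unambiguous.

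The outputs use data already collected. The restricted analysis has fewer women and less precision, conditions on a post-randomisation event, and leaves out the early clinical diagnoses that the protocol deliberately includes. It should be labelled supportive and read with the primary result, not in place of it.
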